### 11.2 Planned recruitment rate

Recruitment of 60 participants into the study will take place online over 16 weeks within a single study site (UNIEXE). Recruitment rate within this timeframe represents a feasibility outcome.

### 11.3 Statistical analysis plan

A detailed statistical analysis plan (SAP) is to be produced; the main points of the statistical analysis are summarised here. All participants will be included in each analysis, separated by arm. Missing data will be reported descriptively. No imputation will be performed due to the feasibility nature of the study, but patterns of missingness will be explored to inform future trial design.

### 11.4 Summary of baseline data and flow of patients

The analysis and presentation of the trial will be in accordance with CONSORT guidelines (Schulz et al., 2010). Recruitment, intervention uptake, outcome completion rates and attrition will be reported (with 95% CIs) and shown on a study flow diagram.

Participants may elect to withdraw from the study if they wish to do so at any time and for any reason (including perceived harms or lack of efficacy of intervention). This can be easily done by discontinuing use of the randomised app.

Participants will be withdrawn from the study entirely if discovered as ineligible at the time of recruitment. As a self-help psychological intervention, we do not anticipate significant iatrogenic effects or side-effects requiring individual discontinuation.

### 11.5 Primary analysis

Primary analyses will be conducted on methodological and feasibility data, such as recruitment rate and source, completion of baseline measures, study attrition etc. For outcomes related to study feasibility (see Table 10).

### 11.6 Secondary analyses

Will be undertaken on either the PHQ-9 or GAD-7, the WSAS and MAUQ (see Table 12 for administration timepoints).

### 11.7 Outcome reporting

Continuous outcomes will be reported descriptively (mean and standard deviation (SD). To explore potential effect sizes and confidence intervals, inferential comparisons will be reported between the two conditions (1) IonaFFV; (2) Iona SHAM CONTROL (control).

### 11.8 Interim analysis and criteria for the premature termination of the trial

No interim analyses are planned. If during second screening the participant records >1 PHQ-9 Q9, they will be directed to the SOS screen where details regarding help seeking for risk will be provided, which has been tailored for Armed Forces veterans. They will receive a message indicating that the app is not suitable to meet their needs and encouraged to contact one of the organisations identified. In order to detect potential harm, all occasions where participant score on item 9 of the PHQ-9 has elevated to 2 or 3 will be recorded by the Lead Researcher as an Adverse Event (AE). Elevation will result in classification as an Adverse Event and result in trial discontinuation for the participant.

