### 8.12 Withdrawal criteria

At any time, participants can choose whether they want to stop using the IonaFFV or Iona SHAM CONTROL intervention, or if they want to withdraw from the trial completely (including all assessments). A log will be kept of the participant number and date of all withdrawals from the trial. Participants who met the inclusion criteria at baseline will not be replaced. Participants that did not meet the criteria at baseline can be replaced and their data removed from the data set. Participants who withdraw from the trial will not be followed up. Once a participant withdraws from the study, they will still be able to use the app until the end of the study period if they choose.

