### 12.2 Risk management processes

As part of our policy for addressing risk and prioritising the welfare of participants there are 2 main processes in place.

The main indicators of harm will be completion of the PHQ-9 questionnaire by the participants in both study arms at all assessments (baseline, 6 weeks, 10 weeks). The PHQ-9 study questionnaire will be automatically screened by the AI function of the apps for signs of distress (defined as scores above 20 on PHQ-9 for depression or reports >1 on Question 9 of the PHQ-9). Outside of the research there is also a function within the apps to identify aspects of risk and through the SOS button, which if selected will automatically provide participants with recommended advice and signpost towards help (e.g. NHS and Armed Forces specific support services).

We will record all occasions where risk within IonaFFV or Iona SHAM CONTROL app has been highlighted and recorded and reported to the Trial Management Group and Sponsor to determine whether events are related to the treatments and to take appropriate action.

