### 13.4 University of Exeter Qualtrics page at second screening (as baseline), 6 and 10 week follow up

A recruit may indicate risk on the website during the baseline assessment or 6 weeks treatment end or 10 weeks follow up in response to questions about suicidality. If the participant scores 2 or 3 on the PHQ-9 Q9, the participant will be encouraged to seek support from family or friends, GP or signposting information to NHS or female Armed Forces signposting information will be provided.

PHQ-9-Q9

Over the last two weeks, how often have you been bothered by any of the following problems? Thoughts that you would be better off dead, or of hurting yourself in some way?

Those scores would represent the answers several days (1), more than half the days (2) and nearly every day (3)

If the potential participant answers yes to either more than half the days (2) or nearly every day (3) to either question, then they would be removed from the trial and automatically presented with the following risk screen:

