Because the study is focused on managing excessive worry or low mood rather than treating current difficulties, this study is not suitable for you. The Iona mobile phone app has not been designed to help with these difficulties so we are sorry to say that taking part in the study would not be in your best interests at this time. Thank you for your interest.

**We strongly recommend contacting your GP or family doctor as the best person to decide what help you need**.

In addition to your GP or if you don’t feel that you can talk to your GP, there are many useful services and useful sources of support.

We hope that you find one or more of the following helpful:

- **Emergency Services** If you need help and it’s an emergency call: 999
- **NHS 111** If you need help now and its not an emergency call: 111
- **Op Courage** An NHS mental health specialist service designed to help serving personnel due to leave the military, reservists, armed forces veterans and their families. Contact: [[contact]](mailto:[contact]) Call: [name]
- **Papyrus [name] or text: [name]** offers National support to young people up to age 35 who are feeling suicidal. (Monday-Friday 10:00am-5:00pm and 7:00pm-10:00pm; 2:00pm-5:00pm on weekends, [[contact]](mailto:[contact])
- The **Samaritans** **[name]**  Freephone (UK and Republic of Ireland): [name] (24 hours) offer a confidential service so you can talk about your feelings, you can contact them at [www.samaritans.org](http://www.samaritans.org), Email: [[contact]](mailto:[contact])
- **SANE** offers support to anyone coping with mental illness, including concerned relatives or friends. The SANE helpline **[name]** is available 7 days a week from 6.pm-11 pm
- **Maytree** is a registered charity supporting people in suicidal crisis and is open for calls and emails 24 hours a day. **– [name],** [[contact]](https://www.bipolaruk.org/)
- There are a series of NHS self-help guides which can be found here <https://web.ntw.nhs.uk/selfhelp/>
- There are more guides and online courses here: <https://www.cci.health.wa.gov.au/Resources/Looking-After-Yourself>

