In the event a participant indicates suicide risk at end of treatment or 6 week follow up (10 weeks) and this screen is displayed, an automated report/record from the website will be sent to the Lead Researcher and logged by them. The record will show the trial number and the answers to the 3 risk questions. This data will monitor frequency of suicidality across the trial arms.

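### The PHQ-9 item 9 stopping rule does not separate stopping the app from stopping assessments, so women flagged at week 6 may give no week-10 data

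*Protocol*

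**What the plan says.** Section 11.8 sets the rule for a participant whose item 9 score rises to 2 or 3: "Elevation will result in classification as an Adverse Event and result in trial discontinuation for the participant". The object of the discontinuation is the trial, not the app.

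Section 13.4, whose heading covers second screening and the 6- and 10-week follow-ups, says of those scoring 2 or 3: "then they would be removed from the trial and automatically presented with the following risk screen". That screen includes the words "rather than treating current difficulties, this study is not suitable for you". The closing paragraph of 13.4 confirms that it can appear after randomisation, since it describes what happens when "a participant indicates suicide risk at end of treatment or 6 week follow up (10 weeks) and this screen is displayed". The resulting records have a stated purpose: "This data will monitor frequency of suicidality across the trial arms".

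Section 8.12 lets a participant choose between stopping the app and leaving the trial with all its assessments. For those who leave it says "Participants who withdraw from the trial will not be followed up", and adds that "they will still be able to use the app until the end of the study period if they choose".

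On harm, section 12.2 says "The main indicators of harm will be completion of the PHQ-9 questionnaire by the participants in both study arms at all assessments", which it lists as baseline, 6 weeks and 10 weeks. Section 12.4 runs adverse event reporting from first app use to the 10-week follow-up. Section 12.3 gives worsening on the PHQ-9 between weeks 6 and 10 as one example of an adverse event.

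**The concern.** Stopping an intervention and stopping observation are different acts. The first may be right for a participant with new suicidal thoughts, and that clinical judgement is not questioned here. The second removes information about the people for whom harm information matters most.

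The protocol draws this distinction in 8.12, but only for a participant's own choice. For an exit triggered by item 9 it draws none. Staff, or whoever programs the Qualtrics logic, must then decide whether the week-10 link still goes out, and the available text points towards no.

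What is at stake is what happens after the flag. Persistence, recurrence or recovery at week 10 would be unknown for flagged women, and week-10 PHQ-9, GAD-7 and WSAS scores would be missing for a reason tied directly to outcome. If 8.12 were applied literally, a flagged woman could keep using the app while her scheduled questionnaires ceased.

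**Working it through.** The protocol states no figure to reproduce: it has no sample size calculation (11.1) and no expected event rate. The check is mainly a reading of the text, followed by an illustration on assumed counts.

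**Reading the rule by time of flag**

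1. *Flag at second screening.* The woman is ineligible (section 7) and is never randomised. Nothing is lost.
2. *Flag during app use, before week 6.* Section 13.1.2 describes logging, notifying the Lead Researcher and recording an adverse event. It does not mention removal. Week-6 data are at risk only if 11.8 is also applied to in-app flags.
3. *First flag on the week-6 questionnaire.* Her week-6 scores are already in hand. Under 11.8 she leaves the trial. No section says she is still assessed at week 10, and 8.12 points to no follow-up.
4. *First flag on the week-10 questionnaire.* All scheduled data have been collected. Nothing is lost.

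The exposed group is therefore case 3, and the exposed data are its week-10 questionnaires.

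**Illustration**

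Inputs: 30 women per arm, 60 in all (section 5). Assumed, not in the protocol: k = 1, 2 or 3 women in one arm flagged at week 6, no other attrition, and one new flag among the remaining women at week 10.

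- Best week-10 completion in the arm = (30 − k)/30; overall = (60 − k)/60.
- Observed week-10 frequency of item 9 at 2 or 3 = 1/(30 − k).
- Full-arm frequency lies between 1/30 (no removed woman still at 2 or 3) and (1 + k)/30 (all of them), a band of width k/30.

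| k | Completion, arm | Completion, overall | Observed frequency | Possible full-arm frequency | Width (points) |
| --- | --- | --- | --- | --- | --- |
| 1 | 29/30 = 96.7% | 59/60 = 98.3% | 1/29 = 3.4% | 3.3% to 6.7% | 3.3 |
| 2 | 28/30 = 93.3% | 58/60 = 96.7% | 1/28 = 3.6% | 3.3% to 10.0% | 6.7 |
| 3 | 27/30 = 90.0% | 57/60 = 95.0% | 1/27 = 3.7% | 3.3% to 13.3% | 10.0 |

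**Effect on the exploratory week-10 PHQ-9 comparison**

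Further assumptions: SD 5, removed women g = 4 to 8 points worse at week 10 than those who remain, losses in one arm only. With no imputation (11.3), the observed arm mean is too low by (k/30) × g.

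- Smallest: (1/30) × 4 = 0.13 points.
- Largest: (3/30) × 8 = 0.80 points.
- 95% CI half-width = t × 5 × √(1/(30 − k) + 1/30): 2.61, 2.63 and 2.66 points for k = 1, 2 and 3.
- Ratio of bias to half-width: 0.13/2.61 = 5% to 0.80/2.66 = 30%.

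If both arms lose the same number with the same gap, the bias in the difference is nil.

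**The case against.** The strongest reply is that the missing week-10 questionnaire is inferred. No sentence says the link is withheld, and 8.9 describes requests going to participants at both timepoints. Section 8.12 concerns voluntary withdrawal, and its odd result when applied here (app kept, assessments stopped) suggests it was not written for this case. The removal sentence in 13.4 speaks of a potential participant, and the screen closes by thanking the reader for her interest. Both are screening language. The closing paragraph of 13.4, on flags at follow-up, describes display and logging only.

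Much of this stands, and it makes 13.4 weaker support than 11.8. But 11.8 is about a rise in score, which applies to women already in the trial, and it states discontinuation as a result, not an option. Section 8.9 does not say that a discontinued woman still counts as a participant who receives requests. In a suicidality rule, text that must be guessed at is itself worth correcting.

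A second reply is that the harm is already captured. This stands in part. The flag is recorded as an adverse event, item 9 rises are recorded separately (12.4), in-app logging may continue if she keeps the app (13.1.2), drop-out reasons are collected (section 5), and missingness patterns will be explored (11.3). What these do not supply is her scheduled week-10 score.

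A third reply is that ending participation is the cautious choice in a trial that holds no GP details and provides no medical care. That supports stopping the app. It is less clear that it supports ceasing to ask how she is, since the questionnaire is also what triggers the support screen.

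**Conclusion.** The point holds in a limited form. Sections 11.8 and 13.4 end trial participation on an item 9 rise without separating app use from assessment. The natural reading leaves women flagged at week 6 without week-10 questionnaires, because of deterioration. That sits badly with 12.2 and with the reporting period in 12.4. Confidence is moderate, because the loss depends on how an unclear rule is applied.

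A reader might infer more than the protocol supports:

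- *That the main harm indicator is lost.* Section 12.2 gives that role to the PHQ-9 at all three assessments. A woman flagged at week 6 has supplied two of them, and the second is where the flag arose.
- *That harm events go uncounted.* The triggering event is recorded as an adverse event. What is missing is the course after it.
- *That the primary timepoint is compromised.* Section 10.4 places it at week 6, which is largely unaffected unless in-app flags also lead to removal, and 13.1.2 does not say they do.
- *That the treatment comparison is seriously biased.* On the assumed counts the bias is 0.13 to 0.80 points, well inside a half-width of about 2.6 to 2.7, and it could be nil.

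The number of women affected is unknown. The counts of 1 to 3 per arm, the SD and the gap are all assumptions, and the completion figures ignore ordinary drop-out. The case rests on incomplete harm follow-up and a cheap remedy, not on a large numerical effect.

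**What to change.** In 11.8, 13.4 and 8.12, state that an item 9 score of 2 or 3 triggers signposting and adverse event recording and may stop app use, but that the remaining scheduled questionnaires are still offered unless the participant withdraws consent. In the version of the risk screen shown at follow-up, remove the paragraph telling her that the study is unsuitable for her, and keep all the support text. Both changes should go to the ethics committee.

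The cost is wording in three sections, one paragraph of one screen and one Qualtrics rule so that later links are still sent. No new data items are needed. The downside is that a few distressed participants receive a further questionnaire, with the support screen shown again if they score 2 or 3. Separate reporting of rule-triggered exits and voluntary drop-out can be left to the SAP.

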### 11.9 Other statistical considerations

Primary and secondary analyses will be performed by the Lead Researcher. The results will be discussed and interpreted prior to the unblinding of group allocation.

### 12. ADVERSE EVENTS

### 12.1 Participant welfare and safety

There is no known health risk associated with any of the assessments or either IonaFFV or Iona SHAM CONTROL. The risk concerning participation in this study is believed to be low. Further, we anticipate that IonaFFV will reduce low mood or worry. In our experience from previous projects, participants are happy to participate and enjoy the assessment tasks. We will strive to use tasks that the participants experience as motivational and reinforcing whenever possible. This will also ensure a low attrition rate.

Because the trial is only focussed on people with mild to moderate depression or anxiety, the initial screening process will exclude anyone with a history of severe psychiatric disorder and those reporting elevated suicidality (PHQ-9>1). These individuals will be automatically guided towards appropriate information and sources of help. This process means that individuals likely to have significantly increased risk (e.g., for self-harm and suicidality), and/or for whom more intensive psychological and psychiatric treatment is appropriate, will not be included in the study.

Other than the intervention failing to produce an effect, there is nothing in the literature to suggest possible adverse effects of the assessments and interventions. As with all psychological interventions, individuals reflect on their difficulties, which can produce temporary increases in distress, but no more than would commonly occur in daily life. Versions of techniques within the intervention are commonly adopted within a general adult version of the Iona app previously employed as in an NHS Talking Therapies for anxiety and depression service and with no detected harmful effect. As such, the intervention within the trial may benefit individual participants. The likeliest outcome for users who do not find the intervention of benefit is their disengagement from it. In addition, all participants receive more intensive monitoring, with processes within IonaFFV and Iona SHAM CONTROL to identify and direct all relevant participants to potential sources of help.

### 12.2 Risk management processes

As part of our policy for addressing risk and prioritising the welfare of participants there are 2 main processes in place.

The main indicators of harm will be completion of the PHQ-9 questionnaire by the participants in both study arms at all assessments (baseline, 6 weeks, 10 weeks). The PHQ-9 study questionnaire will be automatically screened by the AI function of the apps for signs of distress (defined as scores above 20 on PHQ-9 for depression or reports >1 on Question 9 of the PHQ-9). Outside of the research there is also a function within the apps to identify aspects of risk and through the SOS button, which if selected will automatically provide participants with recommended advice and signpost towards help (e.g. NHS and Armed Forces specific support services).

We will record all occasions where risk within IonaFFV or Iona SHAM CONTROL app has been highlighted and recorded and reported to the Trial Management Group and Sponsor to determine whether events are related to the treatments and to take appropriate action.

### 12.3 Definitions

Standard definitions for Adverse Events etc are in Table 13 below. Because the current interventions are digital self-help rather than a medicinal product and involve no biological agent, it is not appropriate to define adverse events etc re any untoward medical occurrence – rather as a psychological intervention, appropriate adverse events would include those related to mental state and behaviour. Furthermore, given the study has no involvement from a mental health or community-based service it will not be possible to record Serious Adverse Events/Reactions or Suspected Unexpected Serious Adverse reactions, only Adverse Events (AEs) captured within the app, or Adverse Reactions (ARs) as determined by the Sponsor can be recorded.

1. Adverse Events (AE) may include significant worsening symptoms of anxiety, worsening symptoms of depression, as operationalized by a deterioration of movement from ‘mild or moderate’ (PHQ-9=>10); to ‘severe’ (PHQ-9=>20) levels of symptoms on the PHQ-9 at 6 weeks assessment or from 6 weeks assessment to 10 weeks assessment.
2. Adverse Reactions (AR) same as AE but where a relationship to the app can be determined.

The following definition is adapted to accommodate the status of the intervention as digital self-help (Table 13).

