### 7. PARTICIPANT INCLUSION/EXCLUSION CRITERIA

**Table 8 Inclusion/Exclusion criteria**

| **Inclusion** | **Exclusion** |
| --- | --- |
| **Initial screening** | |
| Aged 18 or over | AGED <18 |
| Ex-servicewoman | Not ex-servicewoman |
| Resident in Great Britain | Not resident in Great Britain |
| Ability to read and understand English | Unable to read and understand English |
| No history of psychosis, mania, substance/alcohol dependence | History of psychosis, mania, substance/alcohol dependence |
| Ability to download app | Not able to download app |
| Access to smartphone with internet access | No access to smartphone or access internet |
| Not changed or started ADM in last month | Changed or started ADM in last month |
| Not currently receiving mental health support | Currently receiving mental health support |
| **Second screening/Baseline** | |
| PHQ-9=>5; <20 | PHQ-9<5; =>20 |
| GAD7<15 | GAD7=>15 |
| Suicide risk: PHQ-9 Q9=<1 | Suicide risk: PHQ-9 Q9=>2 |

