### 13.1.2 Risk management in trial

Once the participant joins the study and starts to use either of the apps, risk is managed by the participant selecting the SOS button or being directed to the SOS button in the event that either PHQ-9 has increased >1 or score has increased >20. Each occurrence of elevated symptomatology (PHQ-9>20) or risk (PHQ-9-Q9>1) when using either app will be logged by the electronic system, the Lead Researcher notified and recorded as an AE.

We note that the nature of the high level of confidentiality means that we do not have relevant GP or family doctor details for participants. The default response is direct information disclosure to the participant of a potential clinical issue with signposting information provided. Transmission of the collected information to the GP will not be possible and requesting this information a priori would negate the ethical and recruitment benefits of pseudo-anonymity and confidentiality for participants. Based on recent recommendations, our default policy is to inform participants of the possibility of them being at risk and to recommend they seek help. This is to prioritise their welfare.

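### Worsening anxiety is a named adverse event, but no numeric harm rule after randomisation uses the GAD-7, so anxiety-only deterioration has no defined detection criterion

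*Protocol*

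**What the plan says.** Section 12.3 defines adverse events for this trial in these terms: "Adverse Events (AE) may include significant worsening symptoms of anxiety, worsening symptoms of depression, as operationalized by a deterioration of movement from" a PHQ-9 score of 10 or more to one of 20 or more, the latter being severe "levels of symptoms on the PHQ-9 at 6 weeks assessment or from 6 weeks assessment to 10 weeks assessment". The same section restricts what can be entered: "only Adverse Events (AEs) captured within the app, or Adverse Reactions (ARs) as determined by the Sponsor can be recorded".

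Section 12.2 names the safety measure: "The main indicators of harm will be completion of the PHQ-9 questionnaire by the participants in both study arms at all assessments". Its automatic screen for distress is "defined as scores above 20 on PHQ-9 for depression or reports >1 on Question 9 of the PHQ-9". Section 13.1.2 repeats the pair of triggers: "Each occurrence of elevated symptomatology (PHQ-9>20) or risk (PHQ-9-Q9>1) when using either app will be logged by the electronic system", with each occurrence recorded as an adverse event.

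The GAD-7 has a numeric role only at entry. Table 8 sets inclusion and exclusion as "GAD7<15 | GAD7=>15", and section 8.2 uses the PHQ-9 and GAD-7 to direct people at current risk to a feedback screen during second screening. Table 12 collects the GAD-7 at baseline, 6 weeks and 10 weeks. The study summary and the TIDieR table give depression or generalised anxiety disorder as the conditions treated, and section 12.1 describes the population in the same way: "Because the trial is only focussed on people with mild to moderate depression or anxiety".

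**The concern.** The harm definition names two kinds of worsening and measures one. A participant whose anxiety rises sharply while her depression score stays below its cut-off has, on the plain words of section 12.3, had an adverse event. No stated rule would identify it. The protocol treats a GAD-7 of 15 or more as a reason not to enrol, yet gives the same score no safety meaning once the participant is in the trial.

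At stake is the harm record that would accompany any case for a definitive trial. If adverse events are counted by the stated numeric rules, the table by arm describes deterioration in depression and suicidality only. A reader who saw anxiety named in the definition could take the count to cover both conditions.

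**Working it through.** The protocol states no figure to reproduce, since this is a question of definition. The check has three parts.

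**1. Numeric harm triggers after randomisation, side by side**

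| Protocol section | Trigger | GAD-7 term? |
| --- | --- | --- |
| 11.8 | PHQ-9 item 9 rises to 2 or 3 | No |
| 12.2 | PHQ-9 above 20, or item 9 above 1 | No |
| 12.3 | PHQ-9 from 10 or more to 20 or more | No |
| 12.4 | Item 9 from 0 or 1 to 2 or 3 | No |
| 13.1.2 | PHQ-9 above 20, or item 9 above 1 | No |
| 13.4 | Item 9 of 2 or 3 | No |
| 13.5 | PHQ-9 above 20 | No |

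**2. Enumeration of scores**

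Inputs: eligible baseline PHQ-9 of 5 to 19 and GAD-7 of 0 to 14 (Table 8); PHQ-9 maximum 9 × 3 = 27 and GAD-7 maximum 7 × 3 = 21 (Table 11).

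Rule coded from the table above: flag if (baseline PHQ-9 ≥ 10 and follow-up PHQ-9 ≥ 20), or follow-up PHQ-9 > 20, or item 9 ≥ 2.

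- *Does the GAD-7 ever change the flag?* Each item 9 value (0, 1, 2, 3) is compatible with 25 PHQ-9 totals, because the other eight items sum to 0 to 24. That gives 4 × 25 = 100 follow-up states. With 15 baseline PHQ-9 scores there are 15 × 100 = 1,500 combinations. The flag depends on the GAD-7 in 0 of 1,500.
- *Does crossing the entry cut-off on anxiety alone trigger anything?* Hold the PHQ-9 at its baseline value and let the GAD-7 move from 0–14 to 15–21: 15 PHQ-9 scores × 15 baseline GAD-7 scores × 7 follow-up GAD-7 scores = 1,575 moves. With item 9 at 0, none is flagged. With item 9 at 1, none is flagged.
- *Example.* Baseline PHQ-9 8 and GAD-7 12; week 6 PHQ-9 12 and GAD-7 21; item 9 at 0 or 1. The follow-up PHQ-9 is below 20, so no numeric rule is met, although the GAD-7 has risen by 21 − 12 = 9 points to the top of the scale.

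**3. Where a GAD-7 score would have to be seen**

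The note to the study summary table says secondary outcomes are gathered on the university's Qualtrics platform. Section 12.3 limits recordable adverse events to those the app captures (or adverse reactions determined by the sponsor), and section 12.4 says all adverse events are recorded within the app. The only questionnaire that section 12.2 has the app screen is the PHQ-9. A high GAD-7 at week 6 or 10 therefore sits in the outcome data with no stated path into the adverse event record.

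**The case against.** A reader might infer that worsening anxiety can never be flagged, or that anxiety events are zero in both arms by construction. The documents do not support that. Table 13 adapts the adverse event definition to cover any worsening of mental state or behaviour, and the participant in the example meets it. The list in section 12.3 is introduced as illustrative rather than closed. Section 12.4 also monitors serious deterioration, section 12.5 has researchers check for events at treatment end or follow-up, Table 9 schedules adverse event assessment at 6 and 10 weeks, and section 12.2 records risk highlighted in either app. The restriction to the app is not applied strictly either: section 11.8 has the Lead Researcher record item 9 elevations, and section 13.4 sends that person a report from the website. Anxiety that worsens together with the PHQ-9 or item 9 would be caught by their rules.

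All of this stands, and it limits the point. None of these routes says what amount of anxiety worsening counts, on which scale, or who looks at the GAD-7 to find it. They allow recording without defining it.

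A second inference would be that an anxiety harm would be reported as absent. That is not established. The GAD-7 is an outcome at both follow-ups, and section 11.7 reports means, standard deviations and comparisons between arms, so a general shift could show there. It is a weak substitute for an individual criterion. In an arm of 30, one participant rising by 9 points moves the mean by 9 / 30 = 0.3 points, and section 11.6 speaks of analysing either the PHQ-9 or the GAD-7.

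Finally, this is a feasibility trial with no sample size calculation and no interim analysis. Every participant must have a PHQ-9 of at least 5, while no GAD-7 minimum is set. Using the PHQ-9 as the main harm indicator is a defensible choice. It does not explain naming anxiety as an adverse event and then measuring it with a depression scale.

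**Conclusion.** The point holds as an inconsistency in the harm definition. Section 12.3 names worsening anxiety as an adverse event, no numeric rule after randomisation uses the GAD-7, and anxiety-only deterioration therefore has no defined detection criterion. Counts by arm would tend to miss it, although the non-numeric routes mean that some events could still be recorded. The claim is confined to the period after randomisation, because the GAD-7 does have a cut-off at entry.

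The gap in the rules is complete (0 of 1,500 combinations depend on the GAD-7), but the number of participants affected cannot be derived from the protocol, which gives no rate of anxiety deterioration. As an illustration only, if 5% to 10% of the 60 participants crossed the entry cut-off during follow-up, that would be 0.05 × 60 = 3 to 0.10 × 60 = 6. Fewer would go uncounted if some also met a PHQ-9 rule or were recorded under the general wording.

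The feasibility objectives are not threatened. The affected part is the harm summary by arm.

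**What to change.** Reconcile sections 12.2, 12.3, 12.4 and 13.1.2 and Table 13 with Table 12, so that the anxiety event named in section 12.3 is operationalised for recording on the GAD-7 scores already collected at 6 and 10 weeks. State where such an event is recorded, since the scores are held in Qualtrics while sections 12.3 and 12.4 refer to the app. Report these events by arm beside the PHQ-9-defined ones.

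The criterion is for the trial team to choose. The protocol's own GAD-7 entry cut-off is one available reference, but a bare crossing of 15 would count a move from 14 to 15 and not a move from 0 to 14, so the team should decide how it relates to the word significant in section 12.3. Whether participant signposting in section 13.1.2 changes is also the team's decision. The criterion should be fixed before allocation is unblinded.

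The cost is a short protocol amendment and one more automated flag. No new data are needed. The reported adverse event count may be somewhat higher.
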